## Abstract

**Abstract:**

**Introduction:**

Unruptured intracranial aneurysms (UIA) are common in the adult population, but only a relatively small proportion will rupture. It is therefore essential to have accurate estimates of rupture risk to target treatment towards those who stand to benefit and avoid exposing patients to the risks of unnecessary treatment. The best available UIA natural history data are the PHASES study. However, this has never been validated and given the known heterogeneity in the populations, methods and biases of the constituent studies, there is a need to do so. There are also many potential predictors not considered in PHASES that require evaluation, and the estimated rupture risk is largely based on short-term follow-up (mostly 1 year). The aims of this study are to: (1) test the accuracy of PHASES in a UK population, (2) evaluate additional predictors of rupture and (3) assess long-term UIA rupture rates.

**Methods and analysis:**

The Risk of Aneurysm Rupture study is a longitudinal multicentre study that will identify patients with known UIA seen in neurosurgery units. Patients will have baseline demographics and aneurysm characteristics collected by their neurosurgery unit and then a single aggregated national cohort will be linked to databases of hospital admissions and deaths to identify all patients who may have subsequently suffered a subarachnoid haemorrhage. All matched admissions and deaths will be checked against medical records to confirm the diagnosis of aneurysmal subarachnoid haemorrhage. The target sample size is 20 000 patients. The primary outcome will be aneurysm rupture resulting in hospital admission or death. Cox regression models will be built to test each of the study’s aims.

**Ethics and dissemination:**

Ethical approval has been given by South Central Hampshire A Research Ethics Committee (21SC0064) and Confidentiality Advisory Group support (21CAG0033) provided under Section 251 of the NHS Act 2006. The results will be disseminated in peer-reviewed journals.

**Trial registration number:**

ISRCTN17658526.

Strengths and limitations of this studyThe unruptured intracranial aneurysm (UIA) treatment rate is lower in the UK than in many other high-income countries, which reduces selection bias and allows observation of the true UIA natural history.The large cohort size will allow inclusion of more covariates in prediction models than has been possible in previous studies including rare, but salient, patient groups such as those with autosomal dominant polycystic kidney disease.The UK has uniform medical coverage and given virtually all patients who suffer subarachnoid haemorrhage seek medical help, the strategy to use national databases for hospital admissions and deaths in a defined population provides a robust method for identification of outcome events with minimal loss to follow-up.This design makes the Risk of Aneurysm Rupture study an order of magnitude larger than previous natural history studies and allows for repeated follow-up and generation of true long-term rupture risk.Identifying rupture events from hospital admissions databases is reliant on diagnosis coding accuracy; this limitation has been mitigated by searching a broad range of possible codes for intracranial haemorrhagic events and subsequent diagnosis verification against original imaging studies.

## Introduction

 Unruptured intracranial aneurysms (UIA) are common in the general population with an estimated prevalence of 2.3%–3.2%.^1 2^ Aneurysm rupture resulting in subarachnoid haemorrhage is much less common with an annual incidence of 9 per 100 000 of the population.^3^ It is estimated that 1.4% of UIA rupture per year.^4^ Subarachnoid haemorrhage is a serious complication of UIA with a mortality rate of up to 67% and half of the survivors are left disabled.^5^ UIA can be prophylactically treated to prevent rupture, however these procedures carry at least a 5% risk of complications.^6^ In the absence of randomised controlled trial (RCT) data, the decision on proceeding to prophylactic treatment is dependent on natural history data. Decisions regarding whether to follow-up untreated patients radiologically also depend on our understanding of these data.

The first natural history study, and the most applicable to the UK population, was the International Study of Unruptured Intracranial Aneurysms (ISUIA).^7^ However, concerns over the data are well documented,^8^ and the generalisability of the results may be undermined by selection bias resulting from a high treatment rate of 71%. Five further natural history studies have been conducted,^9^,^13^ all in different populations with different selection biases and different periods of follow-up, and yielding different results. For example, Juvela *et al*^9^ reported rupture rates of 26% of UIA <7 mm over 30 years compared with 0% in similar aneurysms extrapolated from ISUIA. This difference may reflect a higher risk in the Finnish population or difference in study methodology—it is not known which.

These six studies were combined in an individual patient-level meta-analysis as the PHASES score, which provides an estimate for 5-year rupture risk.^4^ The PHASES score is the best available evidence for UIA rupture risk. However, it has never been externally validated, and particularly given the heterogeneity in the underlying studies, there is an urgent need to do so.

Furthermore, PHASES was limited to the risk factors available for analysis from the underlying studies. There are many more patient and aneurysm features which have been shown to be associated with rupture or that may be hypothesised to predispose to rupture. These range from common modifiable variables like smoking, to rarer non-modifiable ones like family history and autosomal dominant polycystic kidney disease (ADPKD).

One of the main shortfalls of PHASES is that, with one exception, the constituent studies are based on short lengths of follow-up, with the majority of patients followed up just 1 year, which has been used to generate 5-year risks in PHASES. Clinicians further extrapolate PHASES to patient’s lifetime risk which all makes the large assumption that risk does not change over time. Moreover, even if the bleeding risk remains constant over time, any seemingly small inaccuracies in short-term estimates can become very significant when extrapolated over many decades.

We therefore designed a large multicentre longitudinal study of patients with UIAs to address these concerns.

## Methods and analysis

### Objectives

This study has three objectives:

To measure the accuracy of the PHASES score at predicting UIA rupture rates in the UK population.To develop a new, more personalised, predictive model for aneurysm rupture incorporating additional covariates thought to influence risk.To measure aneurysm rupture risk over time periods >5 years.

### Study setting

This is a multicentre study conducted at up to 30 tertiary neurosurgery units in the UK. Patients will be identified by the neurosurgery unit who diagnosed their UIA. Each unit will collect their baseline data on patients’ clinical and aneurysm characteristics from the time of diagnosis. Central searches of hospital admissions databases, and data analysis, will be performed by the coordinating team at University Hospital Southampton NHS Foundation Trust and the University of Oxford. A separate cohort enriched in patients with autosomal dominant polycystic kidney disease will be established using similar methodology, from up to 70 renal units in the UK.

### Study design

The Risk of Aneurysm Rupture (ROAR) study is a longitudinal study that uses a hybrid design of patient identification at regional neurosurgical units and prospectively collected national hospital admissions databases for outcome events. The study will establish a cohort of patients with a UIA and measure how many subsequently ruptured. This observed rupture rate can be compared with a rate estimated by the PHASES score to determine its accuracy.

Each neurosurgery unit in the UK will be invited to search their medical records for patients diagnosed with a UIA. This search method will be tailored by the individual neurosurgery unit based on what records they keep, but search strategies may include: multidisciplinary team (MDT) meeting logs, radiology reports or electronic patient records. The search strategy will be predefined by individual units dependent on their record systems. The maximum date range for identifying patients is documents dated 1 January 2006 to 31 December 2020, however, this period may be shorter for each unit depending on availability of records. Whatever date range is chosen by the unit, it will be predefined and if the patient’s UIA was newly diagnosed during this period it will be classed as *new* and those who were diagnosed before this period but identified from a document during the aneurysm follow-up will be classed as *follow-up*, and their recruitment date recorded as the date of the document from which they were identified. This will minimise the prevalence-incidence (Neyman)^14^ selection bias created by identifying patients diagnosed before the unit’s search period but who survive without rupture to make it into the search period, whereas their counterparts diagnosed at the same time who rupture and die are not identified. It will also allow comparison of rupture risk of newly diagnosed aneurysms and those with known diagnoses. Baseline clinical characteristics and aneurysm characteristics will be collected as per the common data elements for UIA research.^15^ All data collectors will undergo training in coding data elements delivered by the coordinating centre. Collecting baseline data from local medical records allows deeper phenotypic typing and higher data fidelity than using national admission databases.

Patient identifiable details (name, date of birth, post code, NHS/CHI number) will be securely sent by each neurosurgery unit to the coordinating centre for consolidation and linkage to the national databases for hospital admissions. These databases are: Hospital Episode Statistics (HES), Patient Episode Database for Wales (PEDW) and Scottish Morbidity Database (SMD). These databases also link to the Civil Registrations—Death and National Registry Scotland for death records. Patients will be linked to hospital admissions based on International Classification of Diseases 10th Revision (ICD-10) diagnosis codes for intracranial haemorrhages and OPCS4 codes for aneurysm occlusion treatments. These databases record every hospital admission in their respective country and thus using this as the outcome source, combined with death records, will allow identification of every aneurysmal subarachnoid haemorrhage (aSAH) regardless of whether they were managed in a neurosurgery unit, a district general hospital, migrated out of the region in which their UIA was diagnosed, or died in the community. The number of patients with aSAH who are not captured by this method, either because they do not present to hospital or emigrate out of the UK, is expected to be very small. Rupture rates can be adjusted based on national emigration rates.

Patients will be censored if there is any occlusive treatment of the UIA or patient death. Occlusive treatment includes either microsurgical or endovascular techniques either partial or complete. If none of these censoring events are observed, then they will be censored on the day the cohort is submitted to the HES/PEDW/SMD databases.

The ICD-10 codes to be searched for rupture events have been selected in accordance with the UK Biobank stroke research and include: aSAH (I60.1-9), intracerebral haemorrhage (I61.0-9), traumatic subarachnoid haemorrhage (S06.6) and spontaneous subdural haemorrhage (I62.00-I62.02).^16^ The use of codes beyond those for aSAH will capture any hospital admissions for aneurysm rupture which have resulted in other forms of intracranial bleed or have been miscoded.

It is expected that the use of codes beyond that for just aSAH will return many admissions not due to aneurysm rupture. The matched hospital admissions, and death records, will be returned to the coordinating unit who will in turn use pseudonymisation numbers to inform the respective local unit of their patient’s admission for possible aSAH. The local unit will review the imaging studies, discharge summaries and death certificates for these admissions and confirm or refute the diagnosis. Statistical analysis will begin once the diagnosis for all of the matched admissions is confirmed.

The study is currently opening new sites and identifying patients for inclusion. The baseline data collection is planned to finish by 31 July 2023 and the results released no sooner than 31 July 2024. The study end date is currently 31 July 2034 to allow for repeated searching of hospital admissions databases in the future thereby further extending the follow-up period.

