### Outcomes

#### Primary end points

The primary end point is rupture of an untreated UIA at a timepoint at least 1 day following diagnosis. A rupture event is defined as either radiological evidence of aSAH in a distribution consistent with the aneurysm location, CSF spectrophotometry positive for xanthochromia per the local unit’s reference range or death certificate stating subarachnoid haemorrhage in causes of death 1a-c.

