#### Objective 3: long-term rupture rates

All patients, including those who underwent aneurysm occlusion, will be included in time-to-event analysis which will cover the whole duration of available follow-up. This will include Kaplan-Meier and proportional hazards models for univariate and multivariate survival curve fitting. A cumulative hazard plot will be used to assess if rupture risk is constant or varies with time from diagnosis.

Once the cohort is established, funding will be sought for repeated searches at regular intervals (5 yearly) to update models and provide progressively long-term rupture rates.

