## Discussion

Although the natural history of UIA has been previously investigated with multiple prospective cohort studies, the rupture rate has varied significantly between these. The design of the ROAR study addresses many of the criticisms of these previous natural history studies. ISUIA^7^ is the first natural history study and is drawn from a population that is genetically closest to that of the UK. However, its results are subject to selection bias with 71% of their UIA being treated either before inclusion or during follow-up. It is not known if that selection was random or based on a feature associated with risk such as aneurysm irregularity. It is therefore not known how the rupture rates in the remaining potentially lower-risk patients translate to the general population. The UK has a much lower treatment rate of UIA (approximately 20%). This is one of the lowest rates in a high-income country making it the ideal setting for a natural history study. It remains however that there will be some treatments performed during the study which inevitably will produce some selection bias that cannot be eliminated. Other countries with lower treatment rates are likely to also have low availability of imaging and hence much lower case identification limiting the cohort size and introducing different biases.

There is also a risk of selection bias in ROAR arising from the methods employed for patient identification. Patients in whom no MDT, clinic notes or radiology report was created would be effectively excluded. These are also the patients more likely to not undergo treatment. However, our survey of UK neurovascular surgeons suggest it is only a very small minority that are not discussed at MDT or seen in a neurosciences clinic. This was also borne out in pilot studies in the development of the protocol. The timeframe for searching patients within a unit’s available records creates the potential for introducing prevalence-incidence selection bias. The ROAR study will mitigate this by identifying patients as *new* or *follow-up* based on whether or not the UIA was diagnosed during that unit’s search window and use the identifying document dates accordingly.

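### For follow-up patients the recruitment date is the identifying document, but Objective 3 is read by time from diagnosis; the protocol article does not say how the two dates combine

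*Protocol article*

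**What the plan says.** The protocol article, under Study design, splits patients by whether the aneurysm was diagnosed inside the unit's search window (*new*) or before it (*follow-up*). For the follow-up group it has "their recruitment date recorded as the date of the document from which they were identified". The stated purpose is to minimise the "selection bias created by identifying patients diagnosed before the unit’s search period but who survive without rupture to make it into the search period". The same section adds: "It will also allow comparison of rupture risk of newly diagnosed aneurysms and those with known diagnoses". The Discussion repeats the new/follow-up device and says the study will "use the identifying document dates accordingly".

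Other sections count from diagnosis:
- Study setting: units collect "clinical and aneurysm characteristics from the time of diagnosis".
- Primary end points: the event is "rupture of an untreated UIA at a timepoint at least 1 day following diagnosis".
- Objective 3: all patients enter the time-to-event analysis, and "A cumulative hazard plot will be used to assess if rupture risk is constant or varies with time from diagnosis".

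Objective 1 defines when follow-up ends (treatment, death or database search date) but not when it begins. Objective 2 gives absolute risks at 2, 5 and 10 years from the total data set, also without naming an origin. Delayed entry and left truncation are not mentioned.

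**The concern.** For a patient diagnosed before the window, the diagnosis date and the document date are different, possibly by years. The article uses the document date to control selection and the diagnosis date to state the scientific question, and it does not connect them.

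There are two simple ways to proceed without delayed entry, and each goes wrong differently:
- **Restart the clock at the document.** Patients who have already lived for years with a known aneurysm sit at time 0 beside newly diagnosed patients. The horizontal axis is then a mixture, not time from diagnosis, and the baseline age and aneurysm size of the follow-up group are out of date at their time 0.
- **Start the clock at diagnosis and count everything.** The years between diagnosis and document are event-free by construction, because a patient had to survive them to be found.

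What is at stake is mainly Objective 3, which exists to learn whether hazard is constant. The Introduction criticises the existing score for assuming that it is. Any 2-, 5- or 10-year risk presented as risk from diagnosis would be affected too.

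**Working it through.** **Inputs from the article (Sample size).** Low hazard: 51/(1692 × 4.1) = 0.735% per year. High hazard: 60/4010 = 1.50% per year. The article's own figures follow from the low rate: 60 events need 8161 person-years and 1990 patients, as stated; 120 events need 16 323 person-years (stated as 16 332) and 3981 patients. These figures supply only the illustrative hazards; the point does not depend on them.

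**Assumed inputs (not in the article).** Follow-up share f = 10% to 40%. Lag from diagnosis to document uniform, with mean 2 years (0–4) or 5 years (0–10). In the falling case, a first-year hazard of 3%.

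**Method.** Let A be the cumulative hazard in % over the period, averaged over the lag. Pooled A = (1 − f) × A(new) + f × A(follow-up). Risk = 1 − exp(−A/100).

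**1. Clock restarted, constant hazard.** Both groups have A = 5 × 0.735 = 3.675, so the 5-year risk is 3.61%, equal to the truth. There is no bias if hazard is constant and patients are alike in risk.

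**2. Clock restarted, hazard 3% in year 1, then 0.735%.** Truth: A = 3 + 4 × 0.735 = 5.94, risk 5.77%.
- f = 10%, mean lag 2: follow-up patients average 0.5/4 = 0.125 years at the high hazard. A(follow-up) = 0.125 × 3 + 4.875 × 0.735 = 3.958. Pooled A = 0.9 × 5.94 + 0.1 × 3.958 = 5.742, risk 5.58%.
- f = 40%, mean lag 5: 0.5/10 = 0.05 years at the high hazard. A(follow-up) = 0.05 × 3 + 4.95 × 0.735 = 3.788. Pooled A = 0.6 × 5.94 + 0.4 × 3.788 = 5.079, risk 4.95%.
- Apparent year-1 hazard in these two cases: 0.9 × 3 + 0.1 × (0.375 + 0.875 × 0.735) = 2.80%, and 0.6 × 3 + 0.4 × (0.15 + 0.95 × 0.735) = 2.14%, against a true 3.00%.

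**3. Clock restarted, hazard 0.735% rising to 1.5% at year 5.** Truth: 3.61%.
- f = 10%, mean lag 2: on average 2 of the 5 years fall at the higher hazard. A(follow-up) = 3 × 0.735 + 2 × 1.5 = 5.205. Pooled A = 0.9 × 3.675 + 0.1 × 5.205 = 3.828, risk about 3.8%.
- f = 40%, mean lag 5: on average 3.75 of the 5 years. A(follow-up) = 1.25 × 0.735 + 3.75 × 1.5 = 6.544. Pooled A = 0.6 × 3.675 + 0.4 × 6.544 = 4.823, risk about 4.7%.

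The bias is now upward, so its direction is not fixed.

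**4. Diagnosis clock without delayed entry, constant 0.735%.** Truth: 3.61%. Only years after the document can contain an event.
- f = 10%, mean lag 2: 3 of the 5 years on average. Pooled A = 0.735 × (0.9 × 5 + 0.1 × 3) = 3.528, risk 3.47%.
- f = 40%, mean lag 5: 1.25 of the 5 years on average. Pooled A = 0.735 × (0.6 × 5 + 0.4 × 1.25) = 2.573, risk 2.54%.

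**5. Delayed entry.** A simulation of 2,000,000 patients used the falling hazard, 25% follow-up patients and mean lag 5 years, and dropped patients who ruptured before their document.

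| Analysis | Year-1 hazard | 5-year risk |
|---|---|---|
| Truth | 3.00% | 5.77% |
| Diagnosis origin, delayed entry | 2.99% | 5.78% |
| Clock restarted at document | 2.48% | 5.28% |
| Diagnosis clock, no delayed entry | 2.31% | 4.65% |

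**The case against.** The article speaks of a recruitment date. It never calls that date time zero, and it never rules out delayed entry. The document date is exactly what a left-truncated analysis needs, and a condensed article may leave such a detail to the full protocol or analysis plan. A reader might infer that time zero is the document date and that delayed entry will not be used. The text supports neither as a fact, and this point does not assert them. What stands is that the printed sections use two different origins and leave them unreconciled.

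The document-date rule is also more than a label. Person-time that begins at the document contains no immortal time for follow-up patients, the article claims only to minimise the bias, and it plans a comparison of new with known diagnoses. This is a real partial mitigation, but it is not carried into the Statistical analysis section, where Objective 2 uses the total data set and Objective 3 uses all patients.

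A reader might add the two biases together, or extend the charge to all three objectives. The biases belong to mutually exclusive analyses, and the immortal-time version would defeat the stated purpose of the date rule. Only Objective 3 names diagnosis as its axis; Objectives 1 and 2 are touched only if their risks are presented as risks from diagnosis. The outdated baseline values matter only on the restarted clock, since they fit a diagnosis time scale.

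One could also imagine *new* patients first documented years after diagnosis, or found only through the rupture admission. The article describes no such patients and gives no frequency, so this remains speculation. Requiring the document to pre-date any rupture is a cheap safeguard, not evidence that it happens.

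**Conclusion.** The point holds as a conflict of time origins in the printed plan. Entry for follow-up patients is tied to the document, while the Objective 3 axis, the endpoint and the baseline data are tied to diagnosis, and no rule joins them. A restarted clock with pooled groups is harmless only if hazard is constant in a homogeneous population, which is what Objective 3 is meant to test.

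The size is unknown. Across the assumed shares and lags, a restarted clock lowers a true 5-year risk of 5.77% to 4.95–5.58% when hazard falls early, and raises 3.61% to about 3.8–4.7% when it rises later. The alternative, a diagnosis clock without delayed entry, lowers 3.61% to 2.54–3.47%. These illustrations rest on the assumed share, lag and hazard shape; they are not estimates of the bias in this study. The matter should be settled before analysis.

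**What to change.** - For Objective 3, and for any absolute risk stated from diagnosis, use time since diagnosis as the time scale, with delayed entry (left truncation) at the date of the identifying document. Require that document to pre-date any rupture.
- Keep both the diagnosis date and the identifying-document date for every patient. The article states the document-date rule only for the follow-up group. Where the two dates coincide for a new patient, nothing changes.
- Report new patients alone as a sensitivity analysis for Objectives 1 and 2. This keeps the total data set as planned for Objective 2.

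The cost is slightly fewer early person-years and one extra recorded date, otherwise analysis wording. Because baseline collection was planned to finish by 31 July 2023, units should confirm that the second date is held. One limit remains: delayed entry handles survival to the document, but not selection through the exclusion of aneurysms treated before the search period, if treatment tracked risk that is not modelled. The new-only analysis helps to show whether that matters.

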### Statistical analysis

#### Objective 1: PHASES validation

The PHASES study provides the coefficients from their Cox regression model and baseline survival at 5 years which allows the absolute 5-year risk of rupture to be calculated for all patients who are not censored before 5 years. Time to censoring will be calculated (whichever is soonest of the date of treatment, date of death or the HES/PEDW/SMD search date) to ensure 5 years of follow-up if rupture has not occurred. Discrimination will be assessed using Harrell’s C-index of concordance and Royston and Sauerbrei’s D statistic. Calibration will be assessed at the 5-year time point using the method by Royston.^19^ These will be used to calculate the number of SAH events per 5 years for each PHASES score (≤2 to 12+) and expressed as a percentage with 95% CI to compare with the PHASES estimates.

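### Censoring at occlusive treatment is probably informative, and the article names no step to reduce or bound the bias in Objective 3's crude rupture curves or, to a lesser extent, Objective 1's per-score risks

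*Protocol article*

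**What the plan says.** All points are from the Protocol article.

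- **Censoring rule (Study design).** "Patients will be censored if there is any occlusive treatment of the UIA or patient death". Partial and complete occlusion both count.
- **Objective 1.** Time to censoring is "whichever is soonest of the date of treatment, date of death or the HES/PEDW/SMD search date". The article speaks of the "absolute 5-year risk of rupture to be calculated for all patients who are not censored before 5 years", and then reports observed 5-year risk for each PHASES score.
- **Objective 3.** "All patients, including those who underwent aneurysm occlusion, will be included in time-to-event analysis". Read with the censoring rule, treated patients contribute until their treatment date. "This will include Kaplan-Meier and proportional hazards models for univariate and multivariate survival curve fitting". A cumulative hazard plot is to show whether risk is constant over time.
- **Position on the bias (Discussion).** The UK treatment rate is put at about 20%, against 71% in ISUIA. Of ISUIA the article says: "It is not known if that selection was random or based on a feature associated with risk such as aneurysm irregularity". Of this study it says that "there will be some treatments performed during the study which inevitably will produce some selection bias that cannot be eliminated".
- **Data collected.** Baseline clinical and aneurysm characteristics follow cited common data elements (Study design). Treatment is identified through OPCS4 linkage (Study design). Growth is recorded where follow-up imaging exists, and no date for it is described (Secondary end points).

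**The concern.** A crude Kaplan-Meier or cumulative hazard curve that censors at treatment estimates the untreated rupture risk only if patients who go on to treatment would have ruptured at the same rate as those left under observation. The article doubts this for ISUIA and concedes selection bias for its own cohort, but goes no further. Having said that the bias cannot be eliminated, it does not say how it might be reduced.

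Two outputs could mislead. The long-term rupture risks, which the article says patients most want, could be too low. The plot meant to show whether hazard changes with time could fall only because higher-risk patients leave the risk set early. Part of any gap between observed risk and the PHASES prediction could also reflect who was treated.

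**Working it through.** **Inputs from the article**
- Treated: about 20% (Discussion).
- Lower rupture rate: ISUIA, 51/(1692 × 4.1) = 0.735% per year. As a check on the plan's own arithmetic, 60/0.00735 gives about 8,161 years, as stated under Sample size.
- Higher rupture rate: 1.4% per year (Introduction), or 60/4010 = 1.50% in the feasibility data.

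The article gives no figure for the treatment bias, so there is none to reproduce.

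**Assumed inputs**
- Rupture times are exponential with log-normal variation in hazard, SD of the log hazard 0.8 to 1.0.
- Treatment occurs at a mean of 0.5 to 0.75 years.
- Log-odds of treatment are 0.5 to 1.0 per unit of risk where higher-risk patients are favoured, with 0 and −0.5 as contrasts.

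**Hand approximation.** Suppose treatment is early and treated patients have k times the hazard of the others. The curve then reads the untreated group's hazard, while the true mean is (0.8 + 0.2k) times that. The ratio of estimate to truth is 1/(0.8 + 0.2k):
- k = 1: 1.00
- k = 1.5: 1/1.10 = 0.91
- k = 2: 1/1.20 = 0.83
- k = 0.6: 1/0.92 = 1.09

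**Simulation, crude Kaplan-Meier risk divided by true untreated risk** (600,000 patients per scenario, rates 0.735% and 1.4%, SD about 1, mean time to treatment 0.75 years)

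| Who is treated | 5 years | 10 years |
|---|---|---|
| Unrelated to risk | 0.99–1.01 | 1.00 |
| Higher-risk more often | 0.79–0.92 | 0.78–0.92 |
| Lower-risk more often | 1.07–1.09 | 1.07–1.09 |

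In absolute terms, a true 5-year risk of 3.5% reads as 2.7% to 3.2%, and 6.4% as 5.1% to 5.9%. A second set (mean 0.5 years, SD 0.8 to 1.0, rates 0.735% and 1.5%, higher-risk patients favoured) was about 5% to 18% low. Together these give roughly 5% to 20%.

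**Shape of the hazard.** In the second set, the hazard in years 2 to 5 relative to the first three months was 0.94–0.97 without treatment and 0.80–0.91 with selective treatment.

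**What adjustment recovers.** Standardising over 20 strata of the measured risk factor stands in for censoring weights. With higher-risk patients favoured, the 5-year ratio returns to 0.99–1.00 if that factor carries all the selection, but only to 0.84–0.94 if unmeasured risk also drives treatment.

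**Objective 1, within score groups.** Across 11 score groups, with the second set's inputs, the median within-group bias is about 0 to −1% if the score carries the selection. It is about −3% to −10% if the score correlates only 0.7 with true risk.

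**Objective 1, the 5-year restriction.** Take rupture rate λ and censoring rate c, keep early ruptures, and drop patients censored before 5 years:
- events = λ/(λ+c) × (1 − e^(−5(λ+c)))
- kept = events + e^(−5(λ+c))

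With λ = 0.00735 and 20% censored by 5 years, c = −ln(0.8)/5 = 0.0446. Events = 0.0324 and kept = 0.8035, so the proportion is 0.0403 against a true 1 − e^(−5λ) = 0.0361. The factor is 1.12. With 39% censored it is 1.28–1.29.

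Combining this restriction with selective treatment, and assuming other follow-up limits uniform over 2.6 to 17.6 years, the pooled 5-year proportion was −3% to +10% relative to truth. The sign is therefore not fixed.

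**The case against.** **The full protocol or analysis plan may specify weighting.** This stands as far as silence goes: the absence of a weighting method from an article is no finding. The point rests on what the article does state: a fixed censoring rule, the crude curves it feeds, and an admitted bias left there. By contrast, the article names a specific mitigation for prevalence-incidence bias.

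**The direction is unknown.** This stands. A reader might infer that rupture risks will be understated and that PHASES will falsely appear to over-predict. The documents do not support that. The article gives no direction for UK treatment selection, and even for ISUIA it says only that the remaining patients are potentially lower-risk. The 5-year restriction pushes Objective 1 upward. Censoring at death makes one minus Kaplan-Meier exceed the cumulative incidence by a factor of 1.02–1.10 at 5 years (assumed death rate 1% to 4% per year), although that is a different estimand.

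**Much of the analysis already conditions on risk.** This largely stands. Reporting by PHASES score absorbs selection that the score captures. Cox models containing the drivers of treatment need censoring to be independent only given those covariates. The crude curves have no such protection, and selection on features outside PHASES remains within score groups.

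**The bias indeed cannot be eliminated.** Literally true, since unmeasured selection remains. Nor is the problem ignored: a low treatment rate is a stated reason for the UK setting, and censoring at treatment is a standard choice for untreated natural history. None of this prevents measured selection from being reduced.

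**The data may not suffice.** This stands in part. The article does not list every baseline item and describes neither reasons for treatment nor a date of growth. Undated growth in a treatment model could condition on the future.

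**Conclusion.** The concern holds in a limited form. Treatment censoring is probably informative, and Objective 3's crude curves are the main outputs at risk. If higher-risk aneurysms are treated preferentially, with about 20% treated soon after diagnosis, crude 5- and 10-year risks would be roughly 5% to 20% too low in relative terms, and a falling hazard could be partly an artefact. These sizes rest on assumed heterogeneity, timing and strength of selection. Other assumptions give no bias or an upward one.

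For Objective 1 the within-score bias is smaller and the net sign is undetermined, so the pooled 5% to 20% must not be carried over to the PHASES comparison. The multivariable Cox models are largely protected for measured drivers of treatment. Nor should a reader conclude that weighting would remove the bias: it deals with measured selection only.

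**What to change.** 1. Pre-specify inverse-probability-of-censoring weighting for treatment. Use truncated weights from a time-to-treatment model on the collected baseline patient and aneurysm characteristics, including those outside PHASES, and unit. Weighting on the PHASES score alone would add little to per-score reporting.
2. Use growth only if it is dated, and then as a time-varying covariate.
3. Report weighted beside unweighted results for Objective 3's Kaplan-Meier and cumulative hazard curves and for Objective 1's per-score risks and calibration. The gap between them shows the effect of measured selection, whichever its direction.
4. Let the Objective 1 weights also cover other censoring before 5 years, so that the upward effect of the restriction is handled as well.
5. Amend the Discussion to say that measured treatment selection is weighted for and that unmeasured selection remains.

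The cost is analysis code and wording. No new data are needed, unless growth is to be used and its dates have to be obtained. Intervals will be somewhat wider, and weights will be unstable where nearly all patients are treated, hence the truncation.
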